### WP2: nested qualitative assessment of acceptability

An estimated 4–6 participants will be included in eight focus groups, totalling 16–24 patients and 16–24 healthcare professionals. As noted above, the final sample sizes will be determined by data saturation [29].

### WP3: nested assessment of agreement between the use of Vfrac within general practices and self-completion at home

Based on assessment of agreement using Cohen’s kappa, and assuming approximately 30% of Vfrac outputs will be classified as high risk, for a sample size of 60 (20 from each intervention practice), the margins of error from 95% confidence intervals around estimates of kappa in the range 0.8–0.6 (the definition of substantial agreement) would be from 0.16 to 0.22. This level of precision is deemed sufficient for these purposes.

## Outcome measures and outputs

### Study status

Recruitment for the study began in September 2022 and the study is anticipated to be complete by May 2024.

## Discussion

This is the first study to assess a new clinical decision tool to identify which older women presenting to primary care with back pain are at risk of having an existing VFF and should be referred for a spinal radiograph. The FRAX clinical tool is available to identify an individual’s future risk of VFF, but it differs from Vfrac in that it does not give any information on risk of existing VFFs, instead providing a probability of future fracture [30]. The Study of Osteoporotic Fractures (SOF) has identified regression models to predict those with VFFs [31] and concluded that it was better to perform radiographs in all white women aged ≥ 70 with low bone mass. This is unlikely to be a useful strategy, as assessment of bone mass is not carried out at a population level, and spinal radiographs impart a dose of ionising radiation equivalent to an entire year of background radiation [32]. Simple clinical tools to guide osteoporosis management within primary care have proven to be effective, as many (such as FRAX) are in common use in clinical practice today. Vfrac provides a targeted method of identifying those with existing VFF that could run alongside FRAX. The Vfrac decision tool has an area under the curve (AUC) of 0.802 (95% CI, 0.764–0.840) and it identified 93% of those with more than one fracture and two-thirds of those with one fracture [14].

Feasibility work is required before a large study can be designed to investigate the extent to which Vfrac improves the treatment of older people with osteoporosis. Specifically, this feasibility work will help assess the real-world clinical delivery and implementation of Vfrac and address key uncertainties around trial parameters including sample size required for the cluster design (based on numbers of women who attend their GP with backpain as well as an indication of the potential degree of clustering) and length of follow-up required (based on the time it takes from assessment to final management). It will also generate important information to understand the acceptability of Vfrac to healthcare professionals and patients and identify barriers, facilitators and contextual factors that impact on its implementation. In turn, this will help develop a series of recommendations to optimise the Vfrac tool and its delivery. Results from the second nested study will determine whether Vfrac can be used remotely, that is, as a self-completion tool or as part of a remote consultation. In addition, this feasibility study will assess whether appropriate data on resource use can be collected in a future clinical trial to provide a definitive estimate of the cost-effectiveness of Vfrac.

One of the limitations of this feasibility study is that the use of the Vfrac tool will only be evaluated in older women and the data collected would be confined to older women. Further work is being conducted as part of a separate study to determine whether the Vfrac tool can be used to identify vertebral fractures in older men with a similar success rate to older women. We will assess the level of agreement in Vfrac outputs obtained from face-to-face completion with a research nurse and self-completion by men. Semi-structured interviews will also be undertaken to determine if the Vfrac tool is acceptable to men. Another limitation of this study is the recruitment of only six general practices which will offer only limited data that does not account for UK-wide variability in consultation, management and healthcare use for back pain. Therefore, we will collect and analyse anonymized national data acquired from the Clinical Practice Research Datalink to investigate UK-wide variability in consultation, management and healthcare utilisation for back pain in older adults. This will help understand what ‘usual care’ entails for older people with back pain and help plan future testing of the Vfrac tool.

A future parallel group cluster randomized trial will determine the clinical- and cost-effectiveness of Vfrac from the NHS perspective, compared with the standard care of older women with back pain. The stop/go criteria for a future cluster randomized controlled trial informed by this feasibility study will rely on a realistic required sample size (of up to 40 clusters), a realistic required length of follow-up (no greater than 15 months), and evidence that the Vfrac tool is acceptable to healthcare professionals and patients.

In conclusion, this study is being conducted in preparation for a future definitive, cluster randomized controlled trial to fully evaluate the use of the Vfrac decision tool in improving the detection of VFFs in older women presenting to primary care with back pain. Outputs of this study will allow accurate evidence-led development, planning and funding of the future definitive evaluation of the clinical- and cost-effectiveness of Vfrac. If successful, national implementation of Vfrac is likely to identify more of the currently undiagnosed older women with VFFs. By appropriate interventions with medications that reduce their future fracture risk by 30–70%, implementation of Vfrac is likely to have a major benefit in reducing fracture risk within the older population. It would certainly change clinical practice for older women with back pain.

## Data Availability

The data sets generated from this study will be available in the University of Bristol Research Data Repository. Data will be available 6 months following publication of the feasibility study findings. Access to the data will be restricted to ensure that data are only made available to bona fide researchers for ethically approved research projects, on the understanding that confidentiality will be maintained and after a data access agreement has been signed by an institutional signatory.

## Appendix 1. Vertebral fracture clinical decision tool for older women with back pain (Vfrac)—a feasibility study

### Follow-up data collection form: control general practices

(A). Practice name
(B). Date of download
(C). Data required for
  - All women > 50
  - With consultations for back pain since start of study
(D). List of data to download in an anonymised format*

**Table Taba:**

Anonymised ID
Date of birth
Date of initial consultation for back pain *{now called initiating event}*
Details of initiating event
Professional grouping of healthcare worker carrying out initiating event, e.g. doctor, nurse, and first contact physio
List of other consultations within general practice since initiating event
Medications at time of initiating event
Changes in medications since initiating event—with date of change
Referrals to secondary care since initiating event—with date of referral
Radiology referrals since initiating event—with date of referral
DXA referrals since initiating event—with date of referral
Diagnoses since initiating event—with date of diagnosis

*Patient level data to be anonymised by general practices before returning to research team.

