**Fig. 1 Fig1:**
[figure not shown]
The online vertebral fracture screening tool made available for use by general practitioners in three general practices across the West of England Clinical Research Network

**Table 1 Tab1:** Work packages of the Vfrac feasibility study

Work Package (WP)	Vfrac study component	Objective(s)
1	Vfrac implementation within primary care	To optimise integration of the Vfrac decision tool within primary care IT systems and clinical pathways. To determine the length of follow-up (from assessment to final management) that is required for a future trial.
2	Nested qualitative assessment of acceptability of the Vfrac tool	To understand how acceptable Vfrac is to healthcare professionals (providers) and patients (recipients) and identify factors that impact on implementation, including barriers and facilitators to delivery
3	Nested assessment of agreement between the use of Vfrac within general practices and self-completion at home	To decide whether Vfrac can be self-completed at home or whether it needs to be delivered face-to-face for any future trial.

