## WP 1: Vfrac implementation within primary care

For this work package general practices will be recruited and then assigned to either intervention or control by purposeful selection to ensure there is variation in practice size and deprivation levels in both groups. Six general practices will be recruited from the West of England region purposively, to include small and large practices and practices within different Primary Care Networks (PCNs)/clusters, which vary in deprivation as assessed by the Index of Multiple Deprivation. General practices will be approached by the West of England Clinical Research Network, which covers the Integrative Care Boards of: Bristol, North Somerset and South Gloucestershire; Bath and North East Somerset, Swindon and Wiltshire; and Gloucestershire. Using a proforma, baseline data will be collected from all six practice managers to describe their practice (Table 2).

**Table 2 Tab2:** Data collection from six general practices recruited to the Vfrac feasibility study

**Feasibility study of Vfrac implementation within primary care**	**Outputs**
Outcome measures from intervention and control practices 1.1 Descriptives of each practice -Number of registered patients -Number of women ≥ 50 and ≥ 65 -Computer system -Name of PCN/cluster -Other demographic characteristics 1.2 Type of healthcare professional carrying out initial consultation for back pain 1.3 Number and date of consultations by older women with back pain 1.4 Resource use after initial consultation for back pain including -Consultations in primary and secondary care -Referrals including rheumatology, osteoporosis clinics, geriatrics, physiotherapy, pain clinic -Investigations including DXA, radiology -New medication prescriptions 1.5 New diagnoses since initial consultation for back pain Additional outcome measures from intervention practices only: 1.6 Proportion of consultations for back pain where Vfrac was used 1.7 Other consultations where Vfrac was used 1.8 Results of the Vfrac tool completed in primary care	1. Training requirements for healthcare staff 2. IT requirements and options for ideal integration within IT systems 3. Options for ideal integration within clinical pathways 4. Required length of follow-up for any future definitive trial to capture most (> 90–95%) patient journeys 5. Contribution to understanding of ‘usual care’ for patients who consult with back pain in the control practices where Vfrac is not used

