**Table Tabb:**

Anonymised ID
Date of birth
Date of initial consultation for back pain *{now called initiating event}*
Details of initiating event
Professional grouping of healthcare worker carrying out initiating event, e.g. doctor, nurse, and first contact physio
Vfrac unique code (watermark)
Output of Vfrac (recommend X-ray; no X-ray recommended; value)
List of other consultations within general practice since initiating event
Medications at time of initiating event
Changes in medications since initiating event—with date of change
Referrals to secondary care since initiating event—with date of referral
Radiology referrals since initiating event—with date of referral
DXA referrals since initiating event—with date of referral
Diagnoses since initiating event—with date of diagnosis

*Patient level data to be anonymised by general practices before returning to research team.

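### The practice downloads ask for almost nothing before an undefined initial consultation, so new and continuing back pain, and new and already known diagnoses, cannot be told apart

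*Protocol article*

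**What the plan says.** The follow-up forms in Appendix 1 (control practices) and Appendix 2 (intervention practices) of the protocol article itemise the quarterly download. The entry filter for back pain is the same on both: "With consultations for back pain since start of study". Time zero is the "Date of initial consultation for back pain", which the form then calls the initiating event. Other consultations, medication changes, secondary care referrals, radiology referrals, DXA referrals and diagnoses are all requested from that event onwards; for diagnoses the item reads "Diagnoses since initiating event—with date of diagnosis". The only item that records a prior state is "Medications at time of initiating event". Appendix 2 has the same list plus the Vfrac code and its result ("Output of Vfrac (recommend X-ray; no X-ray recommended; value").

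These items feed several WP1 outcomes and outputs. Table 2 lists "1.5 New diagnoses since initial consultation for back pain", resource use after the initial consultation, and a contribution to understanding usual care in the control practices. Table 1 gives a WP1 objective as "To determine the length of follow-up (from assessment to final management) that is required for a future trial". Table 2 wants that length to capture more than 90–95% of patient journeys, and the Discussion makes "a realistic required length of follow-up (no greater than 15 months" one of the stop/go criteria. Patient-level data are anonymised at each practice before they are returned.

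**The concern.** Back pain in older women is often a continuing problem. Some women who enter by consulting after study start will be partway through an episode, and some will already have a coded vertebral fracture or osteoporosis. The forms ask for nothing that would identify either group.

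Three things are at stake:

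- **New diagnoses.** Vfrac is meant to find undiagnosed fractures. If known cases cannot be identified, the count of new diagnoses mixes discoveries with re-entered codes.
- **Resource use and usual care.** A woman imaged or referred shortly before entry appears as one who consulted and was not investigated.
- **Follow-up length.** The time to final management is read from a mixture of new and continuing episodes in unknown proportion.

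Because data leave the practice anonymised, the research team cannot look up the missing history later. It has to be in the search.

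**Working it through.** **Step 1. What each form can show.** Setting the two item lists against four kinds of woman (constructed cases, for illustration):

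| Woman | What happened | What the form returns | Correct? |
|---|---|---|---|
| A | New pain in the study; imaged, fracture coded afterwards | Event, radiology referral, diagnosis | Yes |
| B | Imaged and fracture coded shortly before study start; consults again in the study; not re-coded | Event, no radiology, no diagnosis | Not counted as new (correct), but looks uninvestigated |
| C | As B, but the old code is re-entered after the event | Event, no radiology, a dated diagnosis | No: counted as new |
| D | Pain for months, no work-up; consults in the study, then imaged | Same record pattern as a new episode | Cannot be distinguished from A's type of entry |

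B, C and D are the problem. The medications item would reveal a B or C who already takes bone-protection treatment, but not one who is untreated.

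**Step 2. Meaning of time zero.** The filter is tied to study start; the date item is not. One practice could return the first back-pain consultation since study start, another the first of the episode, before the study. The form does not decide between these, so time zero could differ between practices.

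**Step 3. Effect on follow-up length.** The 15-month limit is a set threshold with no formula behind it, so there is no figure to reproduce. The documents give neither journey times nor the share of women mid-episode. Everything below is therefore assumption, used only to see which way an effect could go.

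Let T be the full journey from first consultation to final management and f the share of entrants who are mid-episode. A mid-episode woman contributes a remaining time R = U × L, where L is T sampled in proportion to its length and U is uniform on (0, 1). Observed time is T with probability 1 − f and R with probability f. The median of T is set at 3 months (assumed). The f = 0 values have closed forms:

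- Weibull, shape 2: scale 3/√(ln 2) = 3.60; 95th centile 3.60 × √(ln 20) = 6.2.
- Exponential: rate ln 2/3 = 0.231; 95th centile ln 20/0.231 = 13.0. R has the same distribution as T, so f cannot matter.
- Lognormal, log-SD 1: 95th centile 3 × e^1.645 = 15.5.

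| Assumed distribution | 95th centile, f = 0 | f = 25% | f = 50% |
|---|---|---|---|
| Weibull, shape 2 | 6.2 | 6.0 | 5.8 |
| Exponential | 13.0 | 13.0 | 13.0 |
| Lognormal, log-SD 1 | 15.5 | 17.6 | 19.7 |

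The lognormal 90th centile goes from 10.8 to 12.0 to 13.2.

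**Step 4. A calendar-time version.** Journeys start uniformly from 36 months before to 12 months after study start. Women already mid-episode enter at their next consultation, with exponential gaps of mean 3 months. With gamma journeys (shape 4, mean 9 months, assumed), 62% of those entering in the first quarter are mid-episode, and true 90th and 95th centiles of 15.0 and 17.4 months read as 13.0 and 15.5 in that group. Over all entrants about a third are mid-episode and the readings are about 14 and 16.4. With gamma shape 2 and mean 6, the first-quarter 95th centile of 14.2 reads as 13.3. With exponential journeys of mean 6 there is essentially no shift.

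Against the 15-month limit, 17.4 and 15.5 both fail, 14.2 and 13.3 both pass, and the lognormal 95th centile fails at every f. Only a 90th centile assumed to lie on the limit itself (15.0, read as 13.0) comes close to a changed decision. With 12 months of collection, values beyond 12 months could not in any case be observed directly.

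**The case against.** A reader might infer that the forms shorten the measured follow-up and so bias the stop/go rule towards proceeding. The documents do not support that. Step 3 shows the sign depends on the shape of the journey-time distribution, which is not given: a rising chance of completion shortens, a constant one does nothing, a heavy tail lengthens. Moreover, Table 1 times follow-up from assessment, and the tool is for any older woman who consults with back pain, with no requirement of new onset. A future trial of that population would also start the clock for continuing cases at their first consultation in the trial. The first in-study consultation may therefore be the right time zero, and making new-episode women the main estimate would describe a narrower group. This objection stands, and it determines which estimate should lead.

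A second tempting reading is that existing diagnoses in general count as new. They do not: the form takes dated diagnoses from the event onwards, so only re-entry causes the error. Its frequency is not stated.

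It is also fair that medications at the event, and possibly the details of that event, give some history; that a fuller protocol or search specification may define terms; and that the Discussion plans a national primary care database analysis of usual care. These soften the point without removing it. The appendices are itemised lists of what to download, medications do not reveal an untreated known fracture, and the national data cannot show which women in these six practices were already diagnosed.

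**Conclusion.** The gap is real and modest. As written, the forms cannot separate new from continuing episodes, or new from previously known vertebral fracture or osteoporosis. This bears on the new-diagnosis outcome through re-entered codes, and on the resource-use and usual-care description through work-up done just before entry. These conclusions rest on the item lists alone and need no simulation. Their size cannot be given, because the documents state neither the share of women with earlier consultations nor how often codes are re-entered.

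For follow-up length, the effect is unknown in size and direction, and no bias in the stop/go decision is shown. What can be said is that the present download gives no means of checking whether the mixture matters. This is a cheap improvement to the data request, not an error that invalidates the design.

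**What to change.** 1. Define the initial consultation, on both forms, as the first back-pain consultation since study start.
2. Add to both forms the date of the most recent back-pain consultation in the 12 months before that event, or none.
3. Add to both forms any earlier coded vertebral fracture or osteoporosis diagnosis, with its date.
4. Count a diagnosis as new only if it was not coded before the initiating event.
5. Keep all women as the main estimate of follow-up length, and show women with no back-pain consultation in the prior year beside it as a sensitivity analysis. Describe resource use with the same split.

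The cost is two more fields in an electronic search that is already planned. The 12-month look-back is a convention, and the sensitivity group will be smaller. The fields flag women with a recent earlier episode; they do not recover the earlier imaging or referrals themselves.

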### Follow-up

Regular data will then be collected on consultations by older women with back pain from all six general practices every 3 months for 12 months. Data will be collected by electronic download to capture type of healthcare professional carrying out initial consultation for back pain, number and date of consultations by older women with back pain, resource use after initial consultation for back pain and new diagnoses since initial consultation for back pain (Appendix 1). In addition, from intervention general practices data will be collected on proportion of consultations for back pain where Vfrac was used, other consultations where Vfrac was used, and results of the Vfrac tool recorded in the medical notes (Appendix 2). Data collected will be anonymised at each general practice to remove patient identifiable details such as name, address and NHS number.

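### The only general referral row on both download forms is limited to secondary care, so community physiotherapy and similar referrals that outcome 1.4 counts have no row and may be missed

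*Protocol article*

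**What the plan says.** Table 2 of the protocol article (WP 1) sets out outcome 1.4, resource use after the initial back pain consultation, for intervention and control practices alike. Its referral item is "Referrals including rheumatology, osteoporosis clinics, geriatrics, physiotherapy, pain clinic". The list is open-ended and carries no restriction on setting. The same outcome also covers "Consultations in primary and secondary care", investigations and new prescriptions.

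The Follow-up section under WP 1 says that the electronic download is to capture "resource use after initial consultation for back pain and new diagnoses since initial consultation for back pain (Appendix 1"), so the appendix form is the stated source for outcome 1.4.

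The forms in Appendix 1 (control practices) and Appendix 2 (intervention practices) carry the same four rows that bear on referrals and contacts:

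- The general referral row, for which a date is also requested, is "Referrals to secondary care since initiating event".
- The imaging row is "Radiology referrals since initiating event—with date of referral".
- The bone density row is "DXA referrals since initiating event—with date of referral".
- The row for contacts inside the practice is "List of other consultations within general practice since initiating event".

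**The concern.** The outcome and the form meant to supply it do not have the same scope. The outcome covers referrals in any setting, while the general referral row covers one setting. A practice that follows the form to the letter could properly leave out a referral to a community physiotherapy service, although physiotherapy is named in the outcome.

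Two stated purposes depend on this row. The first is resource use: the abstract and the Discussion both make it an aim to learn whether such data can be collected well enough for a definitive trial, so the content of the form is part of what is being tested. The second is the WP 1 output on usual care in the control practices, where referral to physiotherapy is one of the routes that the authors themselves list. If practices read the restriction differently, the recorded counts would also differ between practices for reasons unrelated to care.

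**Working it through.** No arithmetic applies. The article states no figure to reproduce and gives no referral rates. The check sets each referral item in outcome 1.4 against the rows of the two forms.

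| Item in outcome 1.4 | Row on the forms that could receive it | Covered? |
|---|---|---|
| Rheumatology, osteoporosis clinic, geriatrics | General referral row (secondary care) | Yes, if the service is hospital based |
| Pain clinic | General referral row (secondary care) | Yes if hospital based; no row if a community service |
| Physiotherapy, treated as secondary care | General referral row (secondary care) | Yes |
| Physiotherapy, delivered within the practice | General practice consultations | The contact, yes; the act of referral, not clearly |
| Physiotherapy, community service outside the practice | None | No |
| Radiology | Own row, no limit on setting | Yes |
| DXA | Own row, no limit on setting | Yes |

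Three observations on the table:

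1. **The restriction carries meaning.** Outcome 1.4 itself separates primary from secondary care when it lists consultations, so the authors use the terms distinctly. The radiology and DXA rows carry no setting limit and the general row does.
2. **The article places some physiotherapists outside secondary care.** First contact physiotherapists appear among the primary care professionals to be invited in WP 2, and as an example of who may carry out the initiating consultation on both forms. This shows that physiotherapy is not solely a hospital service in this setting. It does not show where referrals for physiotherapy go.
3. **The share affected cannot be derived.** If every practice handles physiotherapy as a secondary care referral, 0% of physiotherapy referrals lack a row. If every one goes to a community service, 100% do. Nothing in the article narrows that range.

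**The case against.** The strongest reply is that this is a loose label in a shorthand list. Outcome 1.4 places physiotherapy and pain clinic beside rheumatology and geriatrics, so practices may well file them all as secondary care. Imaging and DXA are covered separately, practice-based physiotherapy contacts can appear as consultations, and usual care is also to be studied in separate national data. All of this stands, and it limits the point to referrals that leave the practice but do not go to secondary care. It does not close the gap: the form still leaves the decision to each practice, and the national data do not test whether this download works.

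A reader might be tempted further than the documents allow:

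- **That physiotherapy referrals will be lost, or recorded as zero.** This needs all physiotherapy to lie outside secondary care and to be coded so. The article does not say that.
- **That follow-up time will be underestimated against the 15-month stop/go limit.** Follow-up length is to rest on the time from assessment to final management. Nothing makes a physiotherapy referral the final step, and the form dates imaging, diagnoses and medication changes.
- **That a shift from physiotherapy to imaging caused by Vfrac would be half counted.** This presumes a between-group effect analysis that the article does not plan. The row is also identical in both groups.
- **That the receiving service would not be recorded.** This reads the list too strictly. On the same reading the diagnosis row would return dates without diagnoses.

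Nor is this merely detail that a journal article leaves to a fuller document. The appendices reproduce the collection forms with itemised lists, and the point concerns what those lists state.

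**Conclusion.** The point holds in a limited form. Outcome 1.4 counts referrals in any setting, but the general referral row on both forms is confined to secondary care, and no other row takes a referral to community physiotherapy or to another service outside secondary care. Such referrals may be missed or recorded inconsistently between the six practices. The direction of any error is towards understating resource use and the usual care description. Its size is unknown and could be nil.

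The conclusion assumes that practices follow the form as printed and that at least some referrals go to services they would not class as secondary care. It is a gap worth closing because the correction is cheap and because adequate collection of resource-use data is itself under test. It does not threaten the study's other outputs.

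**What to change.** In both appendices, replace the general referral row by: *All referrals since initiating event (secondary care, physiotherapy, pain and other community services), with receiving service and date of referral.* Naming the receiving service makes explicit what the row probably already intends and lets the services listed in outcome 1.4 be told apart. The radiology and DXA rows can stay as they are.

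The change can be made at the next three-monthly download. The forms ask for women with back pain consultations since the start of the study and for events since each woman's initiating consultation, so a later download can recover referrals made earlier. If collection has already closed, the amended row should go into the data form for the definitive trial, and the feasibility report should state that referrals outside secondary care may be under-recorded.

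The cost is one line on each of two forms, a slightly wider search in the practice systems, and a little more data to handle.

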**Results:**

This study will evaluate the use and acceptability of Vfrac within primary care and determine if data on resource use can be collected accurately and comprehensively.

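### The WP1 download forms record no date of leaving the practice or of death, so time to final management and resource use cannot be correctly censored from the listed fields

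*Protocol article*

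**What the plan says.** The protocol article reproduces the WP1 collection instruments. Appendix 1 (control practices) is headed "List of data to download in an anonymised format" and has twelve fields. Appendix 2 (intervention practices) has the same twelve plus the Vfrac code and the Vfrac output.

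- **Start of observation:** recorded, as "Date of initial consultation for back pain".
- **What happens next:** "List of other consultations within general practice since initiating event", then medication changes, referrals to secondary care, radiology and DXA referrals, and finally "Diagnoses since initiating event—with date of diagnosis".
- **End of observation:** the only date is in the form header, "Date of download". It applies to the whole extract, not to one woman.

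Under WP 1, Follow-up, data are taken "from all six general practices every 3 months for 12 months". Neither that section nor Table 2 mentions women who die or leave.

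Two aims rest on these data. Table 2 lists the follow-up length that a future trial needs to capture more than 90–95% of patient journeys. The Discussion derives this from the time between assessment and final management and sets a stop/go limit of 15 months. The Abstract says the study will "determine if data on resource use can be collected accurately and comprehensively".

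**The concern.** Time from assessment to final management is a time-to-event quantity. It needs a start, an event, and for each woman without the event, the date up to which she was observed. The forms give the first, allow the second to be sought, and give the third only for women still registered on the download date.

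The forms define the population as women over 50 with a back-pain consultation since study start. They do not say whether the search runs on current registrations or on everyone registered at any time since then. A woman who transfers out therefore either stays in the extract with no further entries or disappears from later extracts. In the first case she resembles a woman with nothing more to record. In the second her follow-up is lost unless the extracts can be linked.

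What is at stake is the follow-up length, which carries a stop/go limit, and the check on completeness of resource use, because a truncated record reads as low use. An analysis plan could set a censoring rule, but it could not apply one to a date that was never extracted.

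**Working it through.** **1. What the listed fields show for four kinds of women**

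| Woman | What the listed fields show |
|---|---|
| Still registered, journey finished | Events, then nothing until the download date |
| Transferred out with an open pathway, kept in the search | Events, then nothing until the download date |
| Transferred out with an open pathway, dropped from the search | Row present in early downloads, absent later |
| Died with an open pathway | One of the two patterns above |

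The first two rows differ only if final management can be recognised as an event in the record. Even then, the date at which the second woman's observation stopped is unknown.

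**2. Inputs.** The 90–95% target (Table 2), the 12 months of downloads (WP 1, Follow-up) and the 15-month limit (Discussion) come from the article. The article gives no exit rate and states no figure that could be reproduced here. All exit rates below are assumptions, and they pool deaths with transfers.

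**3. How many women exit.** Take an exit hazard h per year and uniform entry over 12 months.

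- Share leaving while under observation: 1 − (1 − e^(−h))/h. This is 2.5% for h = 0.05 and 4.8% for h = 0.10.
- Share gone by 15 months: 1 − e^(−1.25h), which is 6.1% and 11.8%.

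These are shares of all women. They should not be set directly against the 5–10% of journeys that may remain open, because many leavers will already have finished.

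**4. Effect on the journey figure if silent records count as finished.** Suppose 10% of journeys are truly open at 9 months.

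- h = 0.10: 10% × e^(−0.75 × 0.10) = 9.3%.
- h = 0.30 among women with open journeys: 10% × e^(−0.75 × 0.30) = 8.0%. This is a deliberately high rate.

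**5. Effect if they count as unfinished.** Assume exponential journey times with 10% open at 9 months, so the completion rate is λ = −ln(0.10)/0.75 = 3.07 per year. With h = 0.10, the share seen to reach final management by 9 months is λ/(λ + h) × (1 − e^(−0.75(λ + h))) = 0.968 × 0.907 = 0.879. The 10% would then read as 12.1%. The error reverses.

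**6. Effect on the follow-up length, silent records counted as finished.** Assume exponential journey times with 95% complete at T months, so λ = −ln(0.05)/T per month. Let a proportion a exit per year independently, so μ = −ln(1 − a)/12 per month. The apparent 95% time is −ln(0.05)/(λ + μ).

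| True 95% time | a = 3% | 5% | 10% | 15% |
|---|---|---|---|---|
| 15 months | 14.8 | 14.7 | 14.4 | 14.1 |
| 18 months | 17.7 | 17.6 | 17.1 | 16.7 |

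The understatement is about 0.2 to 0.9 months when the truth is 15 months, and 0.3 to 1.4 months when it is 18.

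**The case against.** The strongest reply is that the article never says a silent record counts as a finished journey. Follow-up length is tied to an event, final management, so a leaver without that event might equally be classed as unresolved. A reader might infer that leavers become early finishers and that follow-up is therefore always understated; the documents do not support that. This part of the reply stands, and step 5 shows the opposite error.

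A reader might also infer that attrition cannot be estimated at all. That is too strong. Downloads are dated, repeated every 3 months and carry an anonymised ID. If IDs are stable and leavers drop out of the search, a vanished ID places the exit within 3 months, though without the reason. The article states neither condition. For women assessed with Vfrac, the practice could look up the record by its unique code; no such step is described, and it does not reach control practices.

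Death is not lost information in the way a transfer is. After death there is no further management or resource use for a trial to capture, so the pooled rates above overstate the true misclassification.

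Finally, a loss rate is not a promised output. The Discussion bases the future sample size on attendance numbers and clustering, and attrition is not among the stop/go criteria.

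These points limit the size and fix no direction. They do not supply the missing date.

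**Conclusion.** The point holds as a cheap improvement to the collection forms. Followed exactly, the forms leave WP1 without an individual end of observation, so neither time to final management nor completeness of resource use can be correctly censored from the listed fields. This is not a detail lost in condensing the protocol, because the appendices print the forms themselves.

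The likely effect is small. If silent records count as finished, 10% open at 9 months reads as 9.3% at an assumed exit rate of 10% per year, and a true 95% completion time of 15 months reads as 14.1 to 14.8 months at 3–15% per year. If they count as unfinished, the error runs the other way. All of this rests on assumed exit rates that are independent of journey length, and steps 5 and 6 also on exponential journey times.

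A reader might infer a larger bias because frail women both leave more often and have longer pathways. That is plausible, but the documents give nothing to support or size it.

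**What to change.** - Add to both forms: registration status at download, with month and year of, and reason for, end of registration (transfer or death).
- Run the search on women registered at any time since study start.
- Keep each woman's anonymised ID the same across the 3-monthly downloads.
- In the analysis, censor transfers out at the date of exit. Treat death as a competing event that ends the journey and resource use, not as ordinary censoring.
- Report the exit rate by practice as a useful extra input to planning the future trial.

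The cost is one or two coded fields in an existing electronic search and a few lines in the analysis. The downside is slightly more extraction work, and a death date needs care in anonymisation; month and year would be enough.
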